**Methods:**

In this proposed multicenter, single-blinded, randomized controlled trial, 108 patients with mild-to-moderate plaque psoriasis will be randomly assigned to two groups in a 1:1 ratio to receive either internal or external TCM treatment, and 270 patients with severe plaque psoriasis will be randomly assigned to three groups in a 1:1:1 ratio to receive treatment with TCM or WM, or TCM + WM. All enrolled patients will receive 8 weeks of treatment. Follow-up assessments will be done 8 weeks after the treatment. The primary outcome of this study is the evaluation of efficacy and relapse rate, based on the Psoriasis Area and Severity Index, and the secondary outcome measures include determination of the affected body surface area, physician’s global assessment, pruritus scores (determined using a visual analog scale), TCM symptom score, Dermatology Life Quality Index, patient-reported quality of life score and incidence of serious adverse events.

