### Sample size

The sample size for this study was calculated based on the expected value of the efficacy based on the results from previous studies [17, 28]. The efficacy rates for groups A, B, C, D and E were 30.0%, 59.0%, 73.0%, 55% and 88.0%, respectively. The significance level (alpha) was set at 0.05 and the statistical power was 80%. Based on our calculation using the PASW statistical software (V.18.0), a sample size of 43 patients was required for groups A and B and 72 patients for groups C, D and E. However, considering a potential 25% loss of patients during follow-up, we adjusted the total sample sizes of groups A and B to 54 patients and that of groups C, D and E to 90 patients.

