### Statistical methods

All analyses will be performed by applying the SPSS V.21.0, (SPSS Inc., Chicago, IL, USA) statistical software and the data network platform designed by the data management center of Jiangsu Famaisheng Medical Technology. The outcome investigators will be blinded to group allocation. According to the principle of an intention-to-treat analysis, all patients who will be randomized and evaluated according to the efficacy indicators at least once are defined as the full analysis set population, whereas all patients who meet all inclusion and exclusion criteria and deviated from the prescribed dose less than 20% of the regimen are defined as the per-protocol set population. Patients who received treatment one or more times and have at least one safety evaluation will be analyzed in the safety set population. The efficacy measurement will be evaluated mainly by intention-to-treat analysis (full analysis set) and supplemented by per-protocol analysis. The safety evaluation will be analyzed in the safety set population.

If a numerical variable shows normal distribution and the variance is uniform, the statistical description will be expressed as the mean ± standard deviation; the statistical inference will be expressed by the F and S-N-K tests; and the repeated measurement of data analysis of variance will be used for comparison among the groups at multiple time points. In case a numerical variable shows skewed distribution, the median and minimum and maximum values will be used for statistical description; the rank sum test and Nemenyi test will be used for statistical inference, and the generalized estimation equation will be used for comparison among the groups at multiple time points. For categorical variables, the frequency, constituent ratio and rate will be used for statistical description. If the analysis index is unordered, a chi-squared test will be used for statistical inference and, if the analysis index is ordinal, a nonparametric test will be used for statistical inference. The generalized estimation equation will be used for comparison among the groups at multiple time points. Hypothesis testing will be performed using a two-sided test with 95% confidence intervals. A *P* value less than 0.05 indicates statistical significance.

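### The 72 patients per group for C, D and E follows from no comparison at the protocol's own rates, and the stated 80% power does not hold for C v D (about 61%) or E v C (about 64%).

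*Protocol article*

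**What the plan says.** The Sample size section of the protocol article gives the assumed rates: "The efficacy rates for groups A, B, C, D and E were 30.0%, 59.0%, 73.0%, 55% and 88.0%, respectively". It sets the error rates: "The significance level (alpha) was set at 0.05 and the statistical power was 80"%. It then reports the result: "a sample size of 43 patients was required for groups A and B and 72 patients for groups C, D and E". The figures were raised to 54 and 90, "considering a potential 25% loss of patients during follow-up".

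The abstract confirms that 72 and 90 are per-group numbers, since "270 patients with severe plaque psoriasis will be randomly assigned to three groups in a 1:1:1 ratio", which is 90 in each.

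The Statistical methods section fixes the test. For unordered categorical outcomes "a chi-squared test will be used for statistical inference", and "Hypothesis testing will be performed using a two-sided test with 95% confidence intervals".

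The Sample size section does not say whether 72 was derived for a pairwise comparison (and if so which) or for an overall test of the three groups.

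**The concern.** One required size and one power figure are given for a three-arm cohort whose assumed pairwise differences are very unequal: 18 points (C v D), 15 points (E v C) and 33 points (E v D). One sample size cannot give about 80% power for all three, so the reader needs to know which comparison the 80% describes.

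This matters most for E v C. According to the Intervention description, groups C and E both receive active granules and active cupping and differ only in whether NB-UVB is active or placebo. E v C is therefore the only comparison that shows what NB-UVB adds to TCM, while E v D shows what TCM adds to NB-UVB. The stated aim is to optimise the integration of the two and to establish treatment norms. If E v C has clearly less power than a reader would take from the single figure, a non-significant result there could be misread as showing no added value.

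**Working it through.** **Inputs.** Rates: A 30%, B 59%, C 73%, D 55%, E 88%; alpha 0.05; power 80% (Sample size). Two-sided chi-squared test (Statistical methods). Equal allocation.

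**Step 1: reproduce the protocol's figure for A v B.** Unpooled two-proportion formula:

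n per group = (1.96 + 0.8416)² × [p1(1−p1) + p2(1−p2)] / (p1−p2)², where (1.96 + 0.8416)² = 7.849.

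- A v B: 7.849 × (0.2100 + 0.2419) / 0.29² = 7.849 × 0.4519 / 0.0841 = 42.2, so 43.

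This matches the protocol exactly. The pooled-variance version gives 45.

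**Step 2: apply the same formula to the severe cohort.**

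- C v D: 7.849 × (0.1971 + 0.2475) / 0.18² = 7.849 × 0.4446 / 0.0324 = 107.7, so 108 (pooled 111).
- C v E: 7.849 × (0.1971 + 0.1056) / 0.15² = 7.849 × 0.3027 / 0.0225 = 105.6, so 106 (pooled 109).
- D v E: 7.849 × (0.2475 + 0.1056) / 0.33² = 7.849 × 0.3531 / 0.1089 = 25.4, so 26 (pooled 29).

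**Step 3: overall three-group chi-squared test (2 df).** Mean rate = (0.73 + 0.55 + 0.88)/3 = 0.72. Sum of squared deviations = 0.01² + 0.17² + 0.16² = 0.0546. Noncentrality per patient per group = 0.0546 / (0.72 × 0.28) = 0.2708. Power reaches 80% at 36 per group (80.5%). At 72 the noncentrality is 19.5 and power is 98.3%.

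**Step 4: look for another route to 72.** At alpha 0.05 and 80% power, none of these gives 72:

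| Variant | C v D | C v E | D v E |
|---|---|---|---|
| Unpooled | 108 | 106 | 26 |
| Pooled | 111 | 109 | 29 |
| Arcsine | 110 | 106 | 27 |
| Continuity-corrected | 122 | 122 | 34 |
| One-sided 5%, unpooled | 85 | 84 | 21 |
| Bonferroni for three, unpooled | 144 | 141 | 34 |

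**Step 5: power at the stated size** (exact binomial power of the Pearson chi-squared test, two-sided 5%, unadjusted).

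| Evaluable per group | C v D | E v C | E v D |
|---|---|---|---|
| 72 | 61.4% | 63.9% | 99.6% |
| 90 (no loss) | 72% | 73% | 99.9% |

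The pooled normal approximation at 72 gives 61.6%, 62.5% and 99.5%, so the choice of method moves the result by less than 2 points. A one-sided 5% test at 72 would still give only 73% (C v D) and 74% (E v C). If 25% of the 90 were lost, 67 or 68 would remain and power would be about 59% to 61% for both.

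**Step 6: what 72 per group can detect.** Exact power is 80.2% for 55% v 77% and 82.7% for 73% v 91%. Those are differences of 22 and 18 points, against the assumed 18 and 15.

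**The case against.** The strongest reply is that the protocol never ties the 80% to C v D or E v C. Statistical methods lists multi-group procedures, so an overall three-group test is a fair reading, and on that reading 72 per group gives about 98%. E v D is also amply powered. This stands. A reader might infer that the protocol promises only a 1 in 5 chance of missing the E v C benefit; the text does not say so, and the point here does not rest on it. Nor do the documents support calling the cohort under-powered as a whole: that depends on which comparison is primary. The reply does not explain 72, however. On the overall or E v D reading the requirement would be 36 or under 30.

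It can also be said that the protocol does not spell out the cohort's question as the combination beating each component. That too stands. The importance of E v C is inferred from the arms and the integration aim, and C v D is not shown to be a required confirmatory comparison. For that reason no figure for winning all comparisons jointly is relied on here.

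Third, the power figures apply to one binary comparison at one time point, whereas Statistical methods also allows repeated-measures ANOVA or generalised estimating equations. Power under those models could differ. But the sample size is built on binary rates, so the check uses the same model as the claim.

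Finally, this is a condensed article and the derivation may sit in a fuller document. That could supply the missing comparison, but it would not make the printed inputs yield 72.

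**Conclusion.** The concern holds in this form: 72 per group does not follow from the rates, alpha and power printed beside it for any pairwise comparison or for the overall test, although the standard formula reproduces the 43 for A and B. At 72 per group, power is about 98% overall and 99.6% for E v D, but about 61% for C v D and 64% for E v C. The stated 80% is thus too low for one pairwise comparison and too high for two, by roughly 19 and 16 points. Full retention of all 90 would not close the gap.

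This rests on the protocol's rates taken at face value, a two-sided 5% chi-squared test at a single time point, and no multiplicity adjustment. An adjustment would lower pairwise power further: with Bonferroni for three comparisons, to about 45% (C v D) and 46% (E v C).

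**What to change.** In the Sample size section, state which comparison and method the 72 and the 80% refer to. Replace the single figure with power for each comparison at 72 evaluable per group: overall three-group test about 98%, E v D above 99%, E v C about 64%, C v D about 61%. Add that differences detectable with about 80% power are roughly 55% v 77% and 73% v 91%.

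State that E v C and C v D will be reported as differences with 95% confidence intervals, and that a non-significant result in either is not evidence of no added value. E v D should not be made the headline comparison merely because it is well powered; which comparison is primary is for the sponsor to decide on the trial's aim.

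The cost is rewording. No extra patients are needed and the conduct of the trial does not change. The drawback is that the stated power becomes less favourable.

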### Assignment of interventions: allocation

#### Sequence generation

Eligible patients with mild-to-moderate or severe psoriasis will be enrolled at each of the six participating institutions and will be randomized separately. During their second visit, patients with mild-to-moderate psoriasis will be randomly assigned to either group A or group B in a 1:1 ratio, while those with severe psoriasis will be randomly assigned to group C, group D or group E in a 1:1:1 ratio. Randomization will be performed using a computer-generated random assignment sequence through the central layering and block randomization method of SAS software (V.9.4).

#### Concealment mechanism

A unit unrelated to this clinical trial will be designated to package and distribute the drugs (test and control) under the supervision of statisticians. The allocation concealment will be ensured. A randomization code will be released using a data network platform designed by the data management center of Jiangsu Famaisheng Medical Technology, and the random code will correspond to the drug number and external treatment group. Thereafter, the patients will be allocated to the different treatment groups under randomization concealment.

The JYG and corresponding placebo granules that will be used in this trial were prepared by Sanjiu Pharmaceuticals (Hefei, Anhui Province, China). These drugs meet the requirements of Good Manufacturing Practice for Pharmaceutical Products. The placebo granules are similar to the JYG constituents in terms of appearance, weight and taste, with the main constituents being maltodextrin, lactose and a natural edible pigment.

The glass cups that will be used for the moving cupping therapy were obtained from Guandong Glass Products (Haimen City, Jiangsu Province, China). The moving cupping placebo therapy will be performed by drilling a hole on the top of the tank (0.6 cm in diameter). The moving cupping placebo therapy will have a push-and-pull effect on and around the skin lesion but will not produce a negative pressure attraction effect. The standard operating procedure of moving cupping will be in accordance with Part 5, Cupping of the People’s Republic of China Standard G/B21709.5–2008. In both moving cupping therapy and its placebo, we will use white Vaseline as a lubricating matrix. NB-UVB therapy will be performed using an NB UV wave therapy device, and the placebo therapy will be performed by adjusting the dose to 100 mJ/cm^2^. The moving cupping therapy and phototherapy will be performed by trained researchers, and patients will be required to wear an eye patch while the treatment is being performed. Patients in all five treatment groups will undergo similar medical procedures and will be blinded to the allocation. Additionally, it should be noted that the fortnightly clinical evaluation during the treatment period will be evaluated before the moving cupping therapy to ensure that the investigators are blind to the group allocation.

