### Interventions

#### Intervention description

Patients in the TCM internal treatment group (group A) will receive JYG twice daily after meals and moving cupping placebo therapy three times weekly for 8 weeks, while patients in the TCM external treatment group (group B) will receive JYGP twice daily after meals and moving cupping therapy three times weekly for 8 weeks. Patients in the TCM treatment group (group C) will receive JYG twice daily after meals and moving cupping therapy and NB-UVB placebo therapy three times weekly for 8 weeks, while those in the WM treatment group (group D) will receive JYGP twice daily after meals and moving cupping placebo therapy and NB-UVB therapy three times weekly for 8 weeks. In the TCM + WM treatment group (group E), the patients will receive JYG twice daily after meals and moving cupping therapy and NB-UVB therapy three times weekly for 8 weeks.

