#### Moving cupping therapy

According to the body position requirements during the moving cupping therapy, the patient will be asked to take a suitable sitting or lying position. Subsequently, the operator will expose the local skin, select the acupoint location, and apply a small amount of Vaseline oil to lubricate the skin after routine disinfection. Cups of appropriate size with smooth mouths will be used. The operation will start after disinfection. The operator will adhere to the following procedure during the operation: using the left hand to hold a 95% alcohol cotton ball, the operator will ignite the middle and lower sections of the cup. The operator will then take the cup out after moving it in a circle. Next, holding the cup in his right hand, he will quickly place it at the concentrated site of the lesion, pushing it toward the distal end and turning back. These steps will be repeated several times. Patients will be required to wear an eye patch during the entire operation. Slow walking refers to moving the cupping back and forth approximately once per second, whereas fast walking refers to moving the cupping back and forth approximately twice per second. According to the clinical requirements, a combination of light adsorption and slow walking, light adsorption and fast walking, heavy adsorption and slow walking, and heavy adsorption and fast walking should be chosen. The combination of heavy adsorption and fast walking is often used in the lower back or limbs of patients with plaque psoriasis. The cup will be replaced every five times, with an interval of no more than 10 s. Each part of the moving cupping will be positioned on the patient’s skin about 30 times until the local skin appears reddish, red, crimson or purplish.

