#### Moving cupping placebo therapy

The procedure for moving cupping placebo therapy will be similar to the moving cupping therapy. In this operation, the same glass cup will be used except that it will have 6 mm holes drilled in the top. Patients undergoing the moving cupping placebo operation will also need to wear an eye patch during the procedure. After the oxygen combustion in the cup is consumed, the air can enter through the small hole to supplement it; therefore, the negative pressure adsorption force will not be formed. This simulates moving cupping therapy without the therapeutic effect and is similar to mild scraping therapy, leaving a similar reddish mark on the skin (Fig. 2).

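### Rating before the day's cupping cannot ensure assessor blinding, because earlier cupping sessions and all NB-UVB lie outside the rule

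*Protocol article*

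**What the plan says.** All places are in the protocol article.

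- **Concealment mechanism.** The assessor safeguard applies to "the fortnightly clinical evaluation during the treatment period", which "will be evaluated before the moving cupping therapy to ensure that the investigators are blind to the group allocation". It names cupping only.
- **Intervention description.** Group E, for example, receives "moving cupping therapy and NB-UVB therapy three times weekly for 8 weeks". Cupping, real or sham, has the same frequency in all five groups, and NB-UVB, real or sham, in groups C, D and E.
- **Moving cupping therapy.** The operator is to "quickly place it at the concentrated site of the lesion" and to continue "until the local skin appears reddish, red, crimson or purplish".
- **Moving cupping placebo therapy.** The drilled cup is likened to mild scraping, "leaving a similar reddish mark on the skin". Concealment mechanism adds that it "will not produce a negative pressure attraction effect".
- **NB-UVB.** In Concealment mechanism, "the placebo therapy will be performed by adjusting the dose to 100 mJ/cm^2". No rule orders the rating relative to phototherapy. The eye patch masks the patient, not the assessor.
- **Statistical methods** states that outcome investigators will be blinded. The limitations in the **Discussion** say that independent researchers record results to minimise detection bias, and concede that cupping and phototherapy cannot be double-blind.

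**The concern.** *Ensure* is a claim about a procedure, and the procedure does not deliver it. Rating before the day's cupping removes one cue, that session's fresh mark. It leaves any trace of earlier sessions on the skin being scored, and it leaves NB-UVB untouched.

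PASI underlies the primary outcome (efficacy and relapse). In groups A and B it also decides, at week 4, whether a patient stays on the assigned treatment or is switched. If PASI grades redness, as is generally understood although the article does not say so, leftover redness could act in two ways. It could tell the assessor the group, and it could enter the score directly.

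**Working it through.** The plan gives no figure on this point, so the check is mainly a comparison of its own provisions.

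**1. What the rule leaves visible.** Three sessions a week over two weeks is 3 × 2 = 6, so about six sessions fall between ratings. The rule hides only the one due that day. The spacing within a week is not stated. If sessions fall on the same weekdays each week, the three gaps add up to 7 days and average 7/3 ≈ 2.3 days. In whole days the longest gap is at least 3, because 2 + 2 + 2 = 6 falls short of 7. Nothing prevents a rating one day after a session.

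**2. Whether real and sham marks are claimed to match.** The real end point runs through four colours, reddish to purplish. The sham's likeness is claimed for a reddish mark only. The two overlap at the mild end, and no likeness is claimed for the darker colours.

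**3. Which contrasts carry a cue.**

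| Contrast | Cupping differs? | NB-UVB differs? | Covered by the rule? |
|---|---|---|---|
| A v B, to week 4 | Yes | Not given | Same-day cupping only |
| A v B, after week 4 | Less: A patients without PASI 75 move to real cupping | Not given | Same-day cupping only |
| C v D | Yes | Yes | Same-day cupping only |
| D v E | Yes | No | Same-day cupping only |
| C v E | No | Yes | No |

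C and E share real granules and real cupping, so any visible treatment cue between them must come from NB-UVB. As written, the rule allows a rating after that day's phototherapy. For A and B, cupping marks can differ most up to the week-4 rating that triggers the switch.

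**4. How one grade could act at the week-4 threshold (assumed patient).** Take one body region, with redness, thickness and scaling graded 2 + 2 + 2 = 6 at baseline.

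- Area score unchanged, sum falls to 1: 1 − 1/6 = 83%, PASI 75 met. One extra redness grade: 1 − 2/6 = 67%, not met.
- Area score halved: 1 − 0.5/6 = 92%; with the extra grade, 1 − 1/6 = 83%. Both meet PASI 75.

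A single grade can therefore reverse a borderline decision, but need not.

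**5. Scale for a group comparison (assumed shift).** Let the true response rate p be equal in both arms, and let rating error lower one arm's observed rate by s:

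SE = √{[p(1 − p) + (p − s)(1 − p + s)]/n}; rejection rate = 1 − Φ(1.96 − s/SE) + Φ(−1.96 − s/SE).

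Taking n and p from Sample size (43 and group B's 59%; 72 and group C's 73%):

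| Assumed s | n = 43, p = 59% | n = 72, p = 73% |
|---|---|---|
| 5 points | 7.5% | 10% |
| 10 points | 15.5% | 25% |
| 15 points | 29% | 48% |

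For s = 10 points and n = 43: SE = √[(0.2419 + 0.2499)/43] = 0.107, s/SE = 0.94, rejection rate about 15.5%. Nothing in the documents supports any particular s, so these rows give a range and not an estimate.

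**The case against.** The strongest reply is that the plan has already done most of what is feasible. The sham was built to leave a similar mark, the real end point begins at the same colour, the assessors are independent, and the Discussion openly gives up double-blinding. No section says how long marks last. If they fade between sessions, the cupping part of the concern falls away. Procedure order on the day may also stand in the full protocol or operating procedures.

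Much of this stands. The sham weakens the cue, and persistence of marks is an assumption. But independence does not hide what is visible on the skin, and likeness is claimed for one colour of four. The point also does not rest on detail left out of a condensed article. The article states a rule, names only cupping in it, and says that the rule ensures blinding.

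A reader might go further and infer that lesions will carry purple marks at each rating, that the last session is always 2 to 3 days earlier, or that PASI is biased against the active arms. The documents support none of these. Duration and spacing are not given. Direction is open: leftover redness would raise PASI in the arms with real cupping or NB-UVB, while an unblinded assessor's expectations could lower it. After week 4 many A patients may have real cupping too. Sham NB-UVB is a non-zero exposure and the article gives no active dose, so the visible difference between C and E cannot be sized either.

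**Conclusion.** The point holds in a limited form. The timing rule cannot ensure assessor blinding: it hides one session of about six per rating interval and none of the NB-UVB. The article's own limitations claim only to minimise detection bias, which is the defensible statement. The exposed ratings are the on-treatment PASI scores. The week-4 decision in A and B is the most exposed to cupping marks, and C versus E is the contrast that the rule does not protect at all.

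That PASI *may* be unblinded or affected is a fair conclusion; that it *is* biased is not. The size depends on how long marks last, how far real and sham marks differ, and how assessors react, all of which are assumptions here. The calculations show only that a modest differential error would matter at these sample sizes. The change is worth making because it costs almost nothing, not because harm has been shown.

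**What to change.** In Concealment mechanism:

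1. Require each fortnightly rating to be made by the independent assessor before every study procedure that day, meaning cupping and NB-UVB, real or sham.
2. Place the rating at the session that follows the longest gap in that week.
3. Replace *ensure* with wording that the order reduces the risk of unblinding, in line with the Discussion.

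Optionally, as supportive analyses only:

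- Report PASI without the redness component, if the sub-scores are stored. The article does not say that they are. This would not remove an unblinded assessor's influence on the other components.
- Report the first follow-up PASI, already scheduled 4 weeks after treatment ends (week 8 + 4 = 12), when no recent procedure is present. It also reflects durability off treatment and so cannot stand in for the on-treatment result.

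The cost is a minor constraint on visit scheduling. Treatments, number of visits and sample size are unchanged.
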